### Participants

Patients with stable COPD diagnosed at the respiratory medicine department of Yue-Yang Integrative Medicine Hospital Affiliated to Shanghai University of Traditional Chinese Medicine will be invited to participate in the study. Potential participants will be identified from the clinical database and contacted face-to-face or by phone, to assess their basic eligibility for the study. Individuals interested in the study will be scheduled to attend a screening assessment.

The diagnosis of COPD will be confirmed in accordance with the Global Initiative for Chronic Obstructive Lung Disease (GOLD) criteria. Participants will be included if: (1) they have been diagnosed with moderate to very severe COPD (stages II–IV, that is FEV1/FVC < 0.7, FEV1 < 0.8 predicted) [3]; (2) they are between 40 and 80 years of age; (3) they have been clinically stable in the 4 weeks prior to randomization; (4) they have not participated in any organized exercise training (at least twice a week) in the past 6 months; and (5) they are willing to give written informed consent and cooperate accordingly.

The exclusion criteria are: (1) acute exacerbation that requires a change in pharmacological management or hospitalization; (2) coexistence of other chronic respiratory disorders; (3) severe comorbidities including cardiovascular, liver, or kidney disease; (4) skeletal muscle disease or other disease hampering assessment of muscle strength; (5) an open injury affecting the application of surface electromyography (sEMG); or (6) contraindications preventing the assessment of body composition.

### Intervention

All participants will continue with their prescribed medication. They will attend the same weekly educational sessions including on quitting smoking, self-management, and nutrition. In addition, participants in the exercise groups will attend 3 exercise sessions over 2 weeks to become familiar with the intervention programs. During this study time, the participants will be given oral and visual instructions on how to perform the prescribed pulmonary exercises or the exercises with elastic bands and will be given instructions on how to perform the exercises at a Borg CR10 intensity level of between 4 and 6 [23]. In addition, all participants in the exercise groups will receive a teaching video and exercise record book. After each exercise session, participants will be required to record what they have done, including but not limited to time, duration, intensity, and site (home or other).

#### Control group

Participants in the CG will continue with their prescribed medication and will not receive the exercise intervention.

#### Pulmonary exercise group

Participants in the PG will continue with their prescribed medication treatment and receive 3 months of prescribed pulmonary exercise. The PG exercise regimen will comprise sessions twice daily, 7 days per week over 3 months. On Sunday afternoons, the participants will exercise under the supervision and instruction of physiotherapists in a group format. Each of the these sessions will last approximately 60 min and consist of (1) a 10-min warm-up exercise, focusing on the flexibility of the peripheral skeletal muscles; (2) 40 min of prescribed pulmonary exercise consisting of eight characteristics including the “hu” and “si” sounds in *liuzijue*, “pushing up the sky to regulate the triple warmer” and “drawing a bow to shoot a vulture” in *baduanjin*, “the crane actions, including the crane spreading its wings and flying” in *wuqinxi*, and “cross-armed iron staff” in *yijinjing*; and (3) a 10-min cool-down exercise focusing on stretching the peripheral skeletal muscles. Exercise intensity will be self-determined as being between 4 and 6 according to the Borg CR10 scale (meaning patients feel the intensity as somewhat strong to very strong when performing the exercise). Their heart rate will be monitored using a Polar Team^2^ (Polar, Finland).

#### Resistance exercise group

Participants in the RG will continue with their prescribed medication treatment and receive 3 months of exercising with elastic bands. According to previous studies [21, 24], important exercises for the muscle groups of the upper and lower extremities for COPD patients consist of shoulder shrugs (trapezius), straight arm shoulder abductions (deltoid), arm curls (biceps), chest presses (pectoralis major and deltoid anterior), hip abductions (mesoglutaeus), stiff-legged dead lifts (hamstrings), body squats (gluteus maximus and quadriceps), and standing calf raises (gastrocnemius and soleus). These will be performed with elastic bands (Thera-Bands®, Hygenic Corporation, USA) (Table 1). The bands provide a different resistance according to their color: tan (extra thin) < yellow < red < green < blue < black < silver < gold (maximum resistance) [24]. This will allow participants to choose an appropriate exercise intensity when performing the resistance exercise. The RG regimen will comprise three exercise sessions per week over 3 months. On Sunday afternoons, the participants will exercise under the supervision and instruction of physiotherapists in a group format. Each session will span approximately 60 min and consist of (1) a 10-min warm-up exercise focusing on the flexibility of the eight muscle groups; (2) 40 min of exercises with the elastic bands involving the eight muscle groups (8 to 12 repetitions for each muscle group repeated 3 times with 1-min rest intervals); (3) a 10-min cool-down exercise focusing on stretching the eight muscle groups. Exercise intensity will be determined and monitored using the same method as the PG.

**Table 1 Tab1:** Main characteristics and muscle groups when exercising with elastic bands

Characteristics	Muscle groups
Shoulder shrug	Trapezius
Straight arm shoulder abduction	Deltoid
Arm curls	Biceps
Chest press	Pectoralis major and deltoid anterior
Hip abduction	Mesoglutaeus
Stiff-legged dead lift	Hamstrings
Body squat	Gluteus maximus and quadriceps
Standing calf raise	Gastrocnemius and soleus

#### Pulmonary exercise combined with resistance exercise group

Participants in the PRG will continue with their prescribed medication treatment and receive 3 months of pulmonary exercise combined with exercising with resistance bands. The PRG regimen consists of two daily sessions, 7 days per week of pulmonary exercise and three sessions per week of exercising with resistance bands, over 3 months. On Sunday afternoons, that day’s exercises will be performed under the supervision and instruction of physiotherapists using a group format. Each session will span approximately 60 min and consist of (1) a 10-min warm-up exercise focusing on the flexibility of the peripheral skeletal muscle groups; (2) 20 min of prescribed pulmonary exercises like those done by the PG; (3) 5 min of rest, (4) 20 min of exercises with elastic bands like those done by the RG; and (5) a 5-min cool-down exercise focusing on stretching the peripheral skeletal muscle groups.

### Adherence

For patients in the CG, compliance will be quantified by the number of responses to telephone calls conducted once a week by the specialist, with compliance defined as no less than 85%. In other words, there should be no fewer than 11 responses. For patients in the three intervention groups, compliance will be quantified by the completion of the exercise log by patients and attendance at the supervised training sessions in the hospital. Compliance will be defined as no less than 85% of exercise sessions completed.

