### Statistical analysis

SPSS version 23.0 will be used for data management and statistical analysis. A Kolmogorov–Smirnov test will be used to test for normality, and the normality data will be expressed as mean ± standard deviation, while skewed data will be expressed as median and interquartile range. An intention-to-treat analysis will be used for the allocation, irrespective of whether the participant completes the intervention. Missing outcome data will be handled using a mixed-model method. Then a per-protocol analysis will be conducted, which will include only subjects who completed all outcome measures and followed the intervention protocol. Comparisons of baseline differences between groups will be performed using one-way analysis of variance (ANOVA) or a non-parametric test. Training-related effects will be assessed using 2 × 2 ANOVA (group × time). Differences between variables over time (time effect, from baseline to 3 months) in each group will be evaluated using a paired *t*-test or a non-parametric test. For categorical variables, a chi-squared test will be employed to detect differences. A two-tailed *P* value of <0.05 will be considered to be significant. In addition, differing intervention effects on pulmonary function have been found in previous studies [4, 32, 33], and disease severity may be an important contributor. Therefore, a pre-specified subgroup analysis will be performed to investigate the differences in effectiveness according to disease severity.

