The study has some limitations. First, in any study with an exercise intervention, it is difficult to blind the therapists and participants, so there may be a placebo effect leading to biased results. Lack of blinding may also lead to a deviation from the intended intervention, with participants possibly seeking other treatments during the trial; however, methods such as keeping a log of exercise sessions and completing questionnaires on physical activity may be useful in identifying this. Second, the study mainly focuses on a home-based exercise intervention, and participant compliance may be lower than with a supervised outpatient intervention. However, designated staff will contact participants and supervise the extent of intervention through checking their exercise log books and by telephone. Third, the prescribed pulmonary exercise adopted in the study is a form of traditional Chinese exercise, so that knowledge about is restricted geographically, which may hinder its application and promotion. Finally, the participants included in the study are from the same hospital, so the study results will need to be confirmed by a multi-center study.

In conclusion, this article presents the design and protocol of a clinical trial investigating the effects of home-based prescribed pulmonary exercise in patients with stable COPD. The results of this study are expected to confirm the effects of prescribed pulmonary exercise in COPD patients and identify the strengths and shortcomings of prescribed pulmonary exercise, exercising with elastic bands, and a combined exercise program. In addition, the results may provide the basis for new, operable, effective, and home-based COPD PR programs.

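### Control-group compliance is measured by answered telephone calls, which does not capture adherence to usual care and is a poor basis for the per-protocol analysis

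*Protocol article*

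**What the plan says.** **Control condition.** Under Control group, these participants stay on their medication and do not receive the exercise intervention. Under Intervention, every arm also attends the same weekly education.

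**Compliance.** Under Adherence, for the control group (CG), "compliance will be quantified by the number of responses to telephone calls conducted once a week by the specialist". The threshold is 85%, restated as a count: "there should be no fewer than 11 responses". For the three exercise arms the measure is the exercise log plus supervised attendance: "Compliance will be defined as no less than 85% of exercise sessions completed".

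**Per-protocol set.** Under Statistical analysis, an intention-to-treat analysis comes first, with a mixed model for missing outcome data. A per-protocol analysis follows, "which will include only subjects who completed all outcome measures and followed the intervention protocol". That section does not mention the 85% rule or call counts.

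**Detecting other treatment.** Under Intervention, "all participants in the exercise groups will receive a teaching video and exercise record book". The limitations part of the Discussion accepts that unblinded participants may seek other treatment and says that "keeping a log of exercise sessions and completing questionnaires on physical activity may be useful in identifying this".

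**The concern.** A per-protocol analysis is meant to show the contrast among people who received what they were assigned. In an unblinded exercise trial, the main departure to expect in the usual-care arm is that a control starts exercising. The CG rule does not look at that. It records whether the participant could be reached by telephone, which is a measure of contact. In the exercise arms the same word, compliance, measures the assigned behaviour itself.

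If this rule decides who enters the per-protocol set, that set can retain controls who took up exercise and lose controls who kept fully to usual care. The completeness condition is a separate weakness. Because all outcome measures are required, a participant with a valid 6-min walking test (6MWT), a primary outcome, is lost if body composition or surface electromyography, both secondary, is missing.

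**Working it through.** **1. The plan's own cut-off.** Inputs from Adherence: weekly calls, 85%, 11 responses. The number of calls is not stated, so 3 months is taken as 12 or 13 weeks (assumption).
- 12 calls: 0.85 × 12 = 10.2, rounded up to 11. This reproduces the stated count (11/12 = 91.7%; 10/12 = 83.3%).
- 13 calls: 0.85 × 13 = 11.05, rounded up to 12. Here 11/13 = 84.6%, just under 85%, so the count and the percentage agree only for 12 calls.

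**2. What each arm must do to be compliant (85%).**
- Pulmonary exercise group (PG), 14 sessions a week: 0.85 × 168 = 142.8 and 0.85 × 182 = 154.7, so 143 to 155 sessions of about an hour.
- Resistance exercise group, 3 sessions a week: 0.85 × 36 = 30.6 and 0.85 × 39 = 33.15, so 31 to 34 sessions.
- CG: 11 answered calls.

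The exercise arms are selected on the assigned behaviour and CG on reachability.

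**3. What could reveal exercise in CG.** The record book goes to the exercise arms only. The physical activity questionnaire is given to all arms, but it recalls 7 days and is collected at baseline and 3 months. Only the second covers trial time: 7/84 = 8.3% or 7/91 = 7.7% of the period. It is not tied to compliance or to per-protocol status.

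**4. Controls retained despite exercising.** Assume a share c of retained controls exercises and each gains the full 54 m targeted in Sample size. Then the expected PG−CG difference is 54 × (1 − c). Take SD 57 m and 18 per group from the same section. The standard error is 57 × √(2/18) = 19.0 m, and power ≈ Φ(difference/19.0 − 1.96).

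| c (assumed) | Shrinkage | Difference | Power |
|---|---|---|---|
| 0 | 0 m | 54.0 m | 81% |
| 0.1 | 5.4 m | 48.6 m | 73% |
| 0.2 | 10.8 m | 43.2 m | 62% |
| 0.3 | 16.2 m | 37.8 m | 51% |

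The first row agrees with the plan: 18 per group is its own figure for 80% power.

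**5. Controls dropped for missed calls.** Assume each call is answered independently with probability p. The chance of failing is the binomial probability of fewer answers than required. For 12 calls and p = 0.95 it is 1 − (12 × 0.95¹¹ × 0.05 + 0.95¹²) = 0.118. Expected counts are out of 22 controls.

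| p (assumed) | Fewer than 11 of 12 | Fewer than 11 of 13 |
|---|---|---|
| 0.95 | 12% (2.6) | 2.5% (0.5) |
| 0.90 | 34% (7.5) | 13% (2.9) |
| 0.85 | 56% (12.2) | 31% (6.8) |

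The documents give neither c nor p, so both tables show scale and predict nothing.

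**The case against.** A reader might infer that the protocol itself says the per-protocol set keeps controls who exercise and drops those who miss calls. It does not. Statistical analysis asks only that the protocol was followed. Read against the Control group section, that could exclude a control who exercises and keep one who misses calls. The link to the 85% rule is an inference, and detailed per-protocol criteria are often left to an analysis plan that is not shown here. This objection stands as far as wording goes. It does not remove the point, because Adherence fixes an affirmative numerical rule for CG, it is the only operational criterion given, and it does not measure the control condition.

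A reader might also infer that exercise in CG would go unseen. That is too strong. Controls complete the activity questionnaire, and nothing shows that the weekly call records only whether it was answered. What remains is that the questionnaire sees about 8% of the period and that neither source bears on per-protocol status.

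Three further objections have force:
- The 54 m gain is an upper bound. It is the effect targeted for a regimen of 14 sessions a week, and a control exercising less has no documented reason to match it.
- Contamination alone pulls a superiority contrast towards zero and would be present in the intention-to-treat result as well.
- Some unequal selection is inherent in comparing a demanding programme with usual care, and a new CG definition will not remove it.

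The completeness condition is a common restriction and affects all arms, so it is a separate point and adds no weight to the one about telephone calls.

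**Conclusion.** The point holds in a limited form. The CG compliance rule measures contact and not adherence to usual care, and it is the only operational rule available to the per-protocol analysis. If it is used there, contamination left in CG reduces the PG−CG difference by at most c × 54 m, assuming that an exercising control gains no more than the targeted PG effect. The net effect of the different selection rules across arms cannot be signed. Separately, requiring all outcome measures discards valid primary data from a set that is already small.

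A reader might infer that the trial's main result is compromised, or that a bias of 5 to 11 m is to be expected. The documents support neither. The intention-to-treat analysis does not use this rule, the sample-size figures do not depend on it, and no contamination rate is given. This is a worthwhile correction to a supplementary analysis.

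**What to change.** 1. On the weekly CG call already made, ask whether the participant has taken up any exercise or rehabilitation programme, and record the answer.
2. Define CG per-protocol status by not having taken up a regular exercise programme. One candidate cut-off is the protocol's own eligibility threshold, organised training at least twice a week. Because it counts organised training only, informal home exercise should be recorded too, so that its influence can be examined.
3. Keep call response as a measure of contact only.
4. State in Statistical analysis which criterion decides per-protocol membership in each arm.
5. Require, for each per-protocol analysis, only the outcome being analysed at both visits.

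The cost is one extra question on an existing call and per-protocol sets that differ slightly by outcome. Trial status reports that recruitment is still under way, so the information can be collected prospectively. It would be hard to reconstruct reliably afterwards.

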### Outcome measurement

All participants will undergo assessments within 1 week of being enrolled at baseline and at the end of 3 months. The primary outcomes are the pulmonary function test, 30-s arm curl test, and 6MWT. Secondary outcome measures include the Modified Medical Research Council Dyspnea Scale (mMRC), dual-energy X-ray absorptiometry (DXA), respiratory muscle strength test, peripheral skeletal muscle strength, sEMG, and questionnaires.

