**Methods/design:**

This study is a single-blind, randomized controlled trial. A random number table will be generated by an independent person. Each number will be placed in a sealed opaque envelop to blind assignment. All outcome assessors will be blinded to group assignment.

COPD patients between 40 and 80 years of age, with stable medical treatment and no regular participation in regular exercise in the last 6 months will be included. All participants will be recruited from the Respiratory Medicine Department of Yue-Yang Integrative Medicine Hospital Affiliated to Shanghai University of Traditional Chinese Medicine.

All participants will continue to follow their medical treatment. They will be randomly assigned to one of four groups in a 1:1:1:1 ratio: (1) usual care (control group, CG), (2) pulmonary exercise group (PG), (3) resistance exercise group (RG), or (4) combined pulmonary exercise and resistance exercise group (PRG). CG participants will receive medical treatment only. PG participants will perform 60 min of exercise twice a day 7 days a week for 3 months, with 1 day’s exercise per week at hospital under guidance and supervision. RG participants will perform 60 min of resistance exercise once a day, three times a week for 3 months, with 1 day’s exercise per week at hospital under guidance and supervision. PRG participants will perform 60 min of prescribed pulmonary exercise combined with resistance exercise for 3 months.

The outcomes include the isokinetic strength of peripheral skeletal muscle, surface electromyography, 6-min walking distance, 30-s arm curl test, pulmonary function, respiratory muscle strength, dyspnea, body composition, physical activity, quality of life, and Chronic Disease Self-Efficacy Scale.

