Hence, in this study, 3 months of (1) usual care, (2) prescribed pulmonary exercise, (3) exercising with resistance bands, and (4) prescribed pulmonary exercise combined with exercising with elastic bands will be applied as interventions to COPD patients to evaluate the overall effect of prescribed pulmonary exercise on lung function, exercise capacity, skeletal muscle function, quality of life, and psychological function in patients with COPD. The aim of the study is to further clarify the role of prescribed pulmonary exercise in COPD rehabilitation, since it is a simple, fun, easy to learn, operational, and effective intervention for COPD patients. We hypothesize that prescribed pulmonary exercise can significantly improve pulmonary function, exercise capacity, skeletal muscle function, quality of life, and psychological function, and that combined exercise induces additional benefits in COPD patients compared with single exercise methods.

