### Sample size

The sample size was based on detecting a minimum difference of 54 m in the 6MWT [11] between the control group (CG) and the pulmonary exercise group (PG) and used a baseline standard deviation of 57 m [11]. With a power of 80% and an alpha of 5% (two-sided), the minimum sample size per group is 18 to give a total of 72 participants. Assuming a drop-out rate of 20%, the minimum sample size in total is 88 (22 participants in each group). The participants will be recruited to achieve a balanced number of patients with different levels of severity of COPD.

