#### Assessments of basic characteristic

Assessments of basic characteristics mainly check pulmonary function, dyspnea, and body composition.

The pulmonary function test will be undertaken by specialist personnel. The test will be conducted according to American Thoracic Society / European Respiratory Society (ATS/ERS) standards [25]. Participants will be instructed to breathe, and three reproducible measurements each of FEV1, FVC, and maximal mid-expiratory flow will be obtained (Masterscreen-PFT, Jaeger, Germany). The highest value will be recorded and used for analysis.

The symptoms of dyspnea will be assessed using the mMRC, a five-point scale (0–4) of the severity of dyspnea, with a higher score indicating a higher severity [3].

Body composition will be assessed using DXA (DXA Prodigy, GE Lunar, USA). Patients will be instructed to remove metal objects from their clothing and body and lie on a test platform. DXA support software will calculate body composition including appendicular and body fat mass, appendicular and body skeletal muscle mass, and appendicular and body bone density. In addition, their body mass index will be calculated following measurement of their height and weight using digital scales (4643a, TANITA, Japan).

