There are several highlights to this study. First, the prescribed pulmonary exercise is a rearrangement of traditional Chinese exercise and targeted to COPD patients. The effects of this prescribed pulmonary exercise on lung function, respiratory muscle strength, exercise capacity, skeletal muscle function, quality of life, and physical activity on stable COPD patients will be evaluated. Second, the role of prescribed pulmonary exercise in improving skeletal muscle function and exercise capacity will be determined by comparing the effects of pulmonary exercise and an elastic band program. Third, the effect of pulmonary exercise combined with exercising with elastic bands in stable COPD patients will be determined, and the effects compared with a single program to determine whether combined exercise can achieve additional beneficial effects. Fourth, the study will apply comprehensive measurements to evaluate skeletal muscle function in patients with COPD, including isokinetic muscle strength testing, surface myoelectricity, 6MWT, and the 30-s arm curl test. Fifth, a sub-analysis will be performed to investigate if the treatment effects differ in patients with different disease severity to enable the optimization of treatment effects for all patients suffering from the troublesome disease. Finally, the study is in strict accordance with CONSORT guidelines, so that the effects of the prescribed pulmonary exercise can be clearly determined.

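### Three unranked primary outcomes share one P<0.05 rule, while the sample size covers a single test (6MWT, PG versus CG), so the primary false-positive rate is above 5% if any one positive result counts

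*Protocol article*

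**What the plan says.** - **Outcomes.** Under Outcome measurement: "The primary outcomes are the pulmonary function test, 30-s arm curl test, and 6MWT". No order or lead outcome is given.
- **Content of the lung function outcome.** Under Assessments of basic characteristic: "three reproducible measurements each of FEV1, FVC, and maximal mid-expiratory flow will be obtained". None of these variables is singled out, so the primary set has at least five variables: three spirometry variables, the arm curl and the 6MWT.
- **Arms and contrasts.** From the abstract: "They will be randomly assigned to one of four groups in a 1:1:1:1 ratio". The Background ends with the hypothesis that "combined exercise induces additional benefits in COPD patients compared with single exercise methods". The Discussion promises that the combined programme will be evaluated and "the effects compared with a single program to determine whether combined exercise can achieve additional beneficial effects".
- **Test and threshold.** Under Statistical analysis: "Training-related effects will be assessed using 2 × 2 ANOVA (group × time"), and a two-tailed P "value of <0.05 will be considered to be significant". The section states no ranking, no adjustment and no rule on whether one or all primary outcomes must succeed.
- **Sample size.** It is based on a 54 m difference in 6MWT "between the control group (CG) and the pulmonary exercise group (PG"), SD 57 m, 80% power and two-sided alpha 5%. This gives 18 per group, raised to 22 (88 in total) for 20% drop-out.

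**The concern.** The number of primary questions, the error rate allowed for each, and the sample size do not fit together. The sample size calculation treats the trial as having one question, tested once at 5%. The outcome and analysis sections treat it as having several questions of equal standing, each judged at 5%.

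As written, a chance finding in mid-expiratory flow between two exercise arms could be reported as a significant primary effect, with the same status as the one comparison the trial was sized to answer. A null 6MWT result in PG versus CG could likewise sit beside a positive arm curl result, with nothing in the plan to say which decides. The combined-versus-single question is presented as one the trial will settle, yet no power is stated for it.

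**Working it through.** **1. The stated sample size.** With δ = 54, σ = 57, two-sided α = 0.05 and power 0.80:

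n per group = 2 × (1.960 + 0.842)² × (57/54)² = 2 × 7.849 × 1.114 = 17.5, so 18.

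This matches the protocol. At 18 per group, power is 81% by the normal approximation and 78.8% by the noncentral t distribution. The calculation uses the whole 5% for this one test.

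**2. Number of primary tests.** It depends on how two unstated points are read.
- Variables: 3 if the lung function test is reduced to one variable, 5 if all three spirometry variables count.
- Between-arm tests per variable: 1 (PG–CG alone, or one four-group test); 3 (PG–CG, combined arm versus PG, combined arm versus resistance arm); or 6 (all pairs). The analysis is printed as a 2 × 2 ANOVA, which does not fit four groups. It can be read as one group × time test per outcome or as a series of two-group analyses.

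The extremes are 3 × 1 = 3 tests and 5 × 6 = 30 tests.

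**3. Chance of at least one false positive.** For k independent tests it is 1 − 0.95^k: 14.3% for k = 3 and 22.6% for k = 5. Tests that share arms or outcomes are correlated, so the other cases were simulated: four arms of 18, no true effects, normal outcomes, each test at 0.05, at least 20,000 runs. The protocol gives no correlations between outcomes, so 0.3–0.5 is an assumption.

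| Reading | Correlation 0.3–0.5 |
|---|---|
| 3 outcomes, one test each (PG–CG or four-group) | 12–14% |
| 5 variables, one four-group test each | 19–21% |
| 3 outcomes, three hypothesised contrasts | 30–33% |
| 3 outcomes, all six pairs | 44–48% |
| 5 variables, all six pairs | 57–65% |

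Sensitivity to the assumption:
- If the three spirometry variables correlate at 0.8 with each other, the two five-variable rows become about 17–18% and 53–57%.
- If all outcomes correlate at 0.7, the first row is about 11%. This is the lowest figure found, and it is still twice the nominal level.

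**4. Cost of adjusting instead.** Bonferroni over three outcomes for PG–CG gives α = 0.05/3 = 0.0167. Power for 54 m at 18 per group then falls from 78.8% to 62.9% (noncentral t), or from 81% to 67% (normal approximation). Restoring 80% would need 25 per group before drop-out (24 by the normal approximation). A later adjustment would therefore undercut the sample size already fixed.

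**The case against.** **Detail for the analysis plan.** Adjustment methods and post-hoc procedures are often left to an analysis plan, which is not shown, and a general significance level of 0.05 is compatible with adjusted P values. This is fair as far as the lack of a named adjustment goes. It does not remove the mismatch. The article itself fixes several equal primary outcomes and a sample size for one test, and step 4 shows that a later adjustment would cost power the trial has not provided for.

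**The size depends on the reading.** A reader might infer that a false-positive primary result is more likely than not. The documents do not support that. Figures above 50% need five variables and all six pairs, each unadjusted, and the protocol never says that all six pairs are primary. With one test per outcome or variable the figure is about 11–23%.

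**Co-primary outcomes.** A reader might call the three outcomes co-primary. In strict use that means all must be significant, which would not inflate type I error and would lower power instead. The protocol says only that they are primary, so multiple primary outcomes is the accurate term. The inflation applies if any one positive result suffices, which the text neither states nor excludes.

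**Scale of the trial.** This is a single-centre trial whose Discussion says that multi-centre confirmation is needed. That tempers the consequence but does not settle which result is the primary one.

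**Conclusion.** The point holds in this form: several unranked primary outcomes and one flat threshold stand against a sample size for a single test. If any one significant primary result counts, the false-positive rate exceeds 5% under every reading examined. It is about 12–14% at the narrow end, 30–33% for three outcomes over the contrasts in the stated hypothesis, and up to 57–65% at the widest. These figures assume 18 per arm, no true effects, normal outcomes and correlations of 0.3–0.5. The direction does not depend on the correlation, but the size does.

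It would go too far to read the protocol as declaring that any P below 0.05 establishes success, or as making all 30 possible tests primary. It leaves both points open. Nor can the combined-versus-single comparison be called underpowered by a stated amount, because the protocol gives no expected difference for it. What can be said is that no power is stated for a question it says it will determine.

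**What to change.** 1. **Outcome measurement and Statistical analysis.** Name 6MWT at 3 months, PG versus CG, as the single primary test at two-sided 5%, matching the Sample size section.
2. **Remaining outcomes.** Make the 30-s arm curl and the pulmonary function variables secondary, with FEV1 named as the lead spirometry variable.
3. **Other contrasts.** Report the secondary outcomes and the other arm comparisons, including the combined arm versus each single mode, as estimates with 95% confidence intervals, or under a multiplicity adjustment of the sponsor's choice. A fixed testing sequence is possible. Placing the combined-versus-single contrasts early in it would put comparisons with no stated power ahead of arm curl and FEV1, so the order needs thought.
4. **Discussion.** Say that the benefit of combined over single exercise will be estimated, rather than determined.
5. **Registry.** Update the record before the outcome data are analysed. The trial is already recruiting, and only outcome assessors are blinded, so the start of analysis is a clearer cut-off than unblinding.

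The cost is wording and a registry update. No more participants are needed, and the powered test keeps its full 5%. The drawback is that arm curl and pulmonary function lose primary status.
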